[**13.** **Tables** 11](#_Toc141888147)

[a. Baseline characteristics 11](#_Toc141888148)

[b. Primary outcome 12](#_Toc141888149)

[c. Safety outcomes 12](#_Toc141888150)

[d. Secondary outcomes 13](#_Toc141888151)

[**14.** **Figures** 14](#_Toc141888152)

[a. Flowchart of participants 14](#_Toc141888153)

[**15.** **References** 14](#_Toc141888154)

1. **List of abbreviations**

- BTA Botulinum toxin A
- CPP Chronic pelvic pain
- EQ-5D Quality of life questionnaire
- HADS Hospital Anxiety and Depression Scale
- MAPle Multiple Array Probe Leiden
- PCS Pain Catastrophizing Scale
- PFDI-20 Pelvic Floor Distress Inventory 20
- PFIQ-7 Pelvic Floor Impact Questionnaire 7
- PGI-I Patient Global Impression of Improvement
- PISQ-IR Pelvic Organ Prolapse/Incontinence Sexual Questionnaire, IUGA-Revised
- RCT Randomized controlled trial
- QoL Quality of Life
- VAS Visual Analogue Scale

1. **Introduction**
   1. Background

Chronic pelvic pain is common, affecting 15% of women aged 18-50^1^. Pelvic floor muscle spasms resulting in chronic pelvic pain may occur as a primary event or secondary to a physical, psychological or pathological factor. First-line treatment consists of pelvic floor physiotherapy. When first-line treatment fails, more invasive interventions can be done. One previously published intervention is injection with botulinum toxin A (BTA) in the pelvic floor muscles. It produces a localized, partial, and reversible chemical denervation of the muscle which results in localized muscle weakness or paralysis. There is some evidence that injection of BTA in the hypertonic pelvic floor muscles decreases pelvic pain in patients with therapy resistant chronic pelvic pain; however this is not investigated in a randomized controlled trial.

- 1. Objective

The primary objective of this randomized, double-blind, placebo controlled trial was to compare the effect of BTA injections vs. placebo injections on pelvic pain in women with chronic pelvic pain.

1. **Endpoints**
   1. Primary endpoints

Decrease of chronic pelvic pain, measured by a decrease in visual analog scale score (VAS score 0-10) with 33% and a patient global impression of improvement score (PGI-I) of 1 or 2 (better or much better) at 26 weeks after injection.

- 1. Secondary endpoints
     1. Subjective outcomes (patient reported outcomes)
- pelvic floor distress inventory (PFDI-20)^2^
- pelvic floor impact questionnaire (PFIQ-7)^2^
- quality of life (EQ-5D)^3^
- painDETECT^4^

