- Standardized physical therapy by an experienced registered pelvic floor physical therapist during the study period
- Deblinding of subjects who did not meet the primary endpoint and offer them a second injection with BTA.
- As part of the Open-label Extension Study, subject will fill in validated questionnaires at 4, 8, 12 and 26 weeks after BTA injection.
- One year follow-up questionnaires will be filled in after the primary BTA/placebo injection or one year after the BTA injection in case of the Open-label Extension Study.
  1. Study medication and preparation

The investigational medicinal product (IMP) will either be Botulinum Toxin Type A 100IU or 0.9% NaCl (placebo).

The BTA and placebo will be supplied from site stock, where it is stored according to Good Distribution Practice (GDP ), recommended respectively in Dutch hospital pharmacies and outpatient clinics. The drugs will become investigational medicinal products only when they are made ready for administration.

The independent health professional, not involved in the study or treatment of the patient, will prepare the syringe with the investigational medicinal product under aseptic conditions just before administration. The independent health professional will dissolve 100IU BTA in 6cc 0.9% NaCl in a syringe or only 6cc 0.9% NaCl in a syringe, depending on the treatment arm. This process will always be verified by a second, independent person (controller) to assure that the process is done correctly.

- 1. Randomization procedure and blinding

Participants were randomly allocated to BTA injection or placebo injection in a 1:1 ratio. The 94 sealed opaque envelopes were randomly divided across the inclusion centres and opened on the day of randomization. The gynaecologist, physical therapist and participant were blinded to the treatment arm. Participants who did not meet the primary endpoint (33% reduction VAS score or PGI-I 1 or 2) were deblinded after 26 weeks. Participants who received placebo injection were offered to participate in our open label extension study and receive BTA injection concurrent with pelvic floor physical therapy.

[figure not shown]

Figure 1. flow-chart RCT

[figure not shown]

Figure 2. flow-chart follow-up studies after ending of RCT: one year follow-up and open-label extension study

- 1. Replacement of individual subjects after withdrawal

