If withdrawal occurs before the injection, these patients will be replaced in order to reach the desired statistical power. If withdrawal occurs during the follow-up period, between injection and before the endpoint of 26 weeks, the data will be censored at the last available time-point. Analyses of available data will be performed in the intention to treat group.

1. **Sample-size**

The ANCOVA procedure^10^ showed that to detect a statistical significant 33% difference in pain scores between the intervention group and the control group, a sample size of 94 individuals was required for this trial (47 per group), with 80% power and assuming a two-sided alpha of 0.05.

1. **Analysis considerations**

To evaluate the effect of BTA on the VAS score during follow-up all statistical analysis will be performed according to intention to treat principle.

- 1. Analysis of groups

The intention-to-treat (ITT) population is the as-randomized population. This will consist of all patients who have given consent and have been allocated to one of the two treatments, irrespective of treatment received.

- 1. Covariates and Subgroups

Subgroup analyses are planned to investigate the possible effect on the outcome of treatment of the following possible pre-defined interaction terms:

- Menopausal status (yes vs. no)
- Negative sexual experience (yes vs. no)
- Depression scale at baseline (HADS) (scale 0-21 points)
- Previous operations (Abdominal/pelvic operation vs other)
- Parity (absolute numbers)
- Use of pain opioids (yes vs. no)
- Sexual activity (yes vs. no)

Subgroup analyses will be conducted by adding an interaction term to the model and testing for the statistical significance of this interaction term. We will subsequently examine the likelihood that we have missed any relevant interaction terms through a likelihood ratio test for all baseline characteristics available.

In version 5 of our statistical analysis plan we added one subgroup to our analysis:

- Duration of CPP (<1 year vs. >1 year)

Furthermore, due to our study design (double-blind randomized controlled trial), we determined that covariates did not add value to our analysis.

- 1. Missing data

We will use mixed models for repeated measurements and its ability to handle missing data effectively. Before analyzing our results using mixed models for repeated measurements, the following questions will be answered:

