- EMG signals will be analysed using mixed models for repeated measurements

The analyses will be performed with IBM SPSS Statistics (version 29, Armonk, New York, United States) and R.

In our version 5 statistical analysis, we found that adjusting for baseline and age did not enhance our analysis, given our study's design as a double-blind randomized controlled trial. Therefore, we removed this adjustment from our statistical analysis plan.

1. **Safety analyses**
   1. Adverse events

Adverse event data will be analysed as allocated (intention-to-treat) and 95% confidence interval will be calculated where possible. We do however not foresee a high number of adverse events and in that case adverse events will be mentioned in a table or the text.

- 1. Deaths, Serious Adverse Events and other significant Adverse events

Death/serious adverse events will be described by treatment group.

1. **Other analyses**

Subgroup analysis mentioned in section 6 is seen as hypothesis generating.

1. **Comparison to study protocol**

The current analysis plan is largely based on the published study protocol^11^. Slight changes were made and these are listed below:

- Not only IBM SPSS Statistics for Windows, Version 26.0. will be used, but also R.
- We will not use Kaplan Meier to estimate the success rates at 26 weeks of follow-up. Instead we will use the mixed models for repeated measurements.

1. **Presentation of study results**
   1. Recruitment

The flow of recruitment of study participants will be presented in the CONSORT flow diagram^12^.

- 1. Protocol violations

All protocol violations will be line-listed by treatment group.

- 1. Baseline characteristics

Baseline characteristics of the total randomized (intention-to-treat) population will be presented following the format of the mock table provided in section 13. Discrete outcomes will be presented using absolute numbers and percentages, while continuous outcomes will be presented as means with standard deviations or medians with interquartile ranges.

- 1. Primary outcome

The primary outcome will be presented for the total population as randomised (intention-to-treat). Data will be presented using absolute numbers with percentages for discrete outcomes. Relative Risk or mean difference will be presented together with 95% confidence interval, and p-value otherwise as appropriate.

- 1. Secondary outcomes

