**Table 3. Primary outcomes.**

| Outcomes | BTA | Placebo | p-value |
| --- | --- | --- | --- |
| **Pain score** | N=xx | N=xx |  |
| Baseline | Mean (95% CI) | Mean (95% CI) |  |
| 4 weeks follow-up  8 weeks follow-up  12 weeks follow-up  26 weeks follow-up  BTA vs placebo*  Primary endpoint: 33% reduction in pain score, No. (%) | Mean (95% CI) Mean (95% CI) Mean (95% CI) Mean (95% CI)  NNN% | Mean (95% CI)  Mean (95% CI)  Mean (95% CI)  Mean (95% CI)  NNN% | X  X |
| **PGI-I** | N=xx | N=xx |  |
| 4 weeks follow-up  8 weeks follow-up  12 weeks follow-up  26 weeks follow-up  BTA vs placebo*  Primary endpoint: PGI-I 1 or 2, No. (%) | Mean (95% CI)  Mean (95% CI)  Mean (95% CI)  Mean (95% CI)  NNN% | Mean (95% CI)  Mean (95% CI)  Mean (95% CI)  Mean (95% CI)  NNN% | X  X |
| Data are presented as mean [95% CI] unless stated otherwise  *Pain score: average pain score last 4 weeks, scale 0-10.  **Based on linear mixed models including all time points except for baseline. Controlling for pain score (average past 4 weeks) at baseline and age at baseline.  *** p value for interaction | | | |

- 1. Secondary outcomes

| Outcome | Baseline n=xx | 26 weeks  n=xx | p-value |
| --- | --- | --- | --- |
| **PainDETECT total score** ^a^ |  |  |  |
| BTA  Placebo  *Botox vs. placebo | Mean (95% CI)  Mean (95% CI) | Mean (95% CI)  Mean (95% CI) | X |
| **Current VAS score^b^** |  |  |  |
| BTA  Placebo  *Botox vs. placebo | Mean (95% CI)  Mean (95% CI) | Mean (95% CI)  Mean (95% CI) |  |
| **EQ5D VAS score^c^** |  |  |  |
| BTA  Placebo  *Botox vs. placebo | Mean (95% CI)  Mean (95% CI) | Mean (95% CI)  Mean (95% CI) | X |
| **HADS depression scale^d^** |  |  |  |
| BTA  Placebo  *Botox vs. placebo | Mean (95% CI)  Mean (95% CI) | Mean (95% CI)  Mean (95% CI) | X |
| **HADS anxiety scale^d^** |  |  |  |
| BTA  Placebo  *Botox vs. placebo | Mean (95% CI)  Mean (95% CI) | Mean (95% CI)  Mean (95% CI) | X |
| **Pain catastrophizing scale (PCS)^e^** |  |  |  |
| BTA  Placebo  *Botox vs. placebo | Mean (95% CI)  Mean (95% CI) | Mean (95% CI)  Mean (95% CI) | X |
| **PFIQ-7 total score^f^** |  |  |  |
| BTA  Placebo  *Botox vs. placebo | Mean (95% CI)  Mean (95% CI) | Mean (95% CI)  Mean (95% CI) | X |
| **PFDI-20 total score^g^** |  |  |  |
| BTA  Placebo  *Botox vs. placebo | Mean (95% CI)  Mean (95% CI) | Mean (95% CI)  Mean (95% CI) | X |
| **PISQ-IR total score^h^** |  |  |  |

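### The 80% power in the sample-size section belongs to a difference in mean pain scores, not to the yes/no responder endpoint declared as primary

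*SAP*

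**What the plan says.** - **Sample size (Section 5).** An ANCOVA procedure is used "to detect a statistical significant 33% difference in pain scores between the intervention group and the control group, a sample size of 94 individuals", "with 80% power and assuming a two-sided alpha of 0.05", that is 47 per group. The cited reference is a sample-size formula for analysis of covariance. No mean, SD, baseline correlation or responder rate is printed.
- **Primary endpoint (Section 3).** Pain decrease at 26 weeks, "measured by a decrease in visual analog scale score (VAS score 0-10) with 33% and a patient global impression of improvement score (PGI-I) of 1" (a score of 2 also qualifies). The passage on randomisation and blinding in Section 4 restates the endpoint with the two parts joined by *or*, and speaks of participants who did not meet it.
- **Mock Table 3 (Section 13).** The row "Primary endpoint: 33% reduction in pain score, No" (%) and a parallel row for PGI-I 1 or 2 are both laid out as counts with percentages. There is no row for the combination.
- **Analysis (Section 7).** The null hypothesis concerns the decrease in pain scores, and VAS is analysed with a mixed model on the scores. No test of the combined responder is named.
- **Presentation (Section 11).** "Relative Risk or mean difference will be presented together with 95% confidence interval, and p-value otherwise as appropriate".

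**The concern.** An ANCOVA formula gives the power to detect a difference in means. A responder endpoint has its own power, which depends on the response rates in the two groups, and Section 5 gives none. The two uses of 33% hide this. In Section 3 it is a cut-off applied to each woman's own change; in Section 5 it is a difference between the groups' pain scores. Neither follows from the other.

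At stake is how a non-significant responder comparison would be read. With only the Section 5 statement to go on, a reader would take it as coming from a trial with 80% power for that comparison, which the plan has not shown.

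**Working it through.** **Inputs from the SAP:** 47 per group, 1:1 allocation, two-sided alpha 0.05, power 80%, ANCOVA on pain scores. **Assumed:** placebo responder rates of 10% to 50%, a normal outcome, and an unadjusted comparison of two proportions.

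**1. The plan's own figure.** The formula is n per group = 2(1.960 + 0.842)² (1 − ρ²)(SD/δ)². It cannot be run forward, because SD, ρ and the mean that would turn 33% into points are not printed. So 94 can be neither confirmed nor refuted. As an illustration, taking δ as 33% of an assumed mean of 6 to 7, SD 2 to 3 and ρ 0 to 0.7 gives 7 to 37 per group.

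**2. The effect implied by 47 per group.** Solving backwards, δ / (SD√(1 − ρ²)) = 2.802 × √(2/47) = 0.578. The noncentral t calculation gives 0.584. This holds for any SD and ρ.

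**3. The same effect as a responder difference.** For placebo rate p0, set p1 = Φ(Φ⁻¹(p0) + 0.584), p̄ = (p0 + p1)/2, and

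power = Φ{[(p1 − p0) − 1.96√(2p̄(1 − p̄)/47)] / √([p0(1 − p0) + p1(1 − p1)]/47)}.

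Example for p0 = 0.40: p1 = Φ(−0.253 + 0.584) = 0.630. The difference is 0.230, the critical value is 1.96 × 0.103 = 0.202, and the standard error is 0.100. Power is 0.61.

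| Placebo rate | BTA rate at 0.584 SD | Power, 47 per group | BTA rate needed for 80% | Difference needed |
|---|---|---|---|---|
| 10% | 24.3% | 45% | 34% | 24 points |
| 20% | 39.8% | 56% | 47% | 27 points |
| 30% | 52.4% | 60% | 58% | 28 points |
| 40% | 63.0% | 61% | 68% | 28 points |
| 50% | 72.0% | 59% | 77% | 27 points |

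The largest power over all cut-points is 60.8% (59.9% with 0.578). The required difference peaks at about 28.5 points, near a placebo rate of 35%.

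**4. Sensitivity.** Step 3 leaves the responder comparison the whole ANCOVA gain, by applying the shift in residual SD. On the raw score scale the shift is 0.578√(1 − ρ²). At an assumed ρ of 0.5 this is 0.50, and the largest power is 48%.

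**5. Larger effects.** A responder difference of 33 percentage points with 47 per group gives 91% to 98% power at placebo rates of 5% to 50%. Sizing two proportions for 33 points needs 24 to 35 per group (29 to 41 with continuity correction), so this is not where 47 came from.

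**The case against.** **The plan is partly continuous.** The null hypothesis and the VAS mixed model in Section 7 concern pain scores and match the sizing, and Section 11 allows a mean difference as well as a relative risk. This stands. It means the mismatch is as much an unclear primary analysis as a power problem. It does not remove the mismatch, because Sections 3 and 4 and Table 3 still call a met-or-not-met outcome the primary endpoint.

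**A reader might infer that the trial has 60% power at best.** The documents do not support that as a general ceiling. It holds only if the true effect is no larger than the one solved back from 47 per group. The SAP does not tie its 33% to 0.58 SD. With δ at 33% of an assumed mean of 6 to 7, SD 2 to 3 and ρ 0.3 to 0.5, simulated power for a 33%-fall responder was 69% to over 99%.

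**A reader might also infer that requiring PGI-I lowers power further by a known amount.** It cannot be quantified. The SAP gives no relation between PGI-I and VAS change, and it joins the two parts by *and* in one place and *or* in another.

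**The missing inputs may be in the protocol.** That is possible, and their absence is not the complaint. No SD or correlation turns the power of a comparison of means into that of a responder comparison.

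**Conclusion.** The point holds as an inconsistency between the sample size and the declared primary endpoint. It is not an arithmetic error: nothing shows that 94 is wrong for the outcome it was calculated for. The 80% belongs to the between-group difference in mean pain score, and the power for the responder endpoint is unstated.

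The range of about 45% to 61% rests on three assumptions: the true effect is the one implied by 47 per group, the outcome is normal, and proportions are compared without adjustment. A 33% relative fall on a 0 to 10 scale meets normality only approximately. The detectable difference of about 24 to 28 points (placebo rates 10% to 50%) does not depend on the first two assumptions and is the safer figure to report.

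**What to change.** In Section 5:

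1. State that the 80% power refers to the between-group difference in mean pain score at week 26.
2. Keep the two uses of 33% apart: the within-woman cut-off of Section 3, and the between-group difference used for sizing, given in points with the mean it is taken from.
3. Add what 47 per group offers for the Section 3 responder endpoint: either the conditional power with its assumptions, or the responder difference detectable with 80% power. The *and* and *or* wordings of the endpoint must be reconciled first, since the figure has to refer to one definition.

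I do not suggest making the mean score primary instead. The SAP describes allocation and deblinding in the past tense, so moving to the better-powered outcome now could be read as outcome switching.

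The cost is wording only, with no extra patients. The downside is a less favourable power statement for the responder endpoint.

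### The 80% power in Section 5 comes from an ANCOVA calculation, but Sections 6 and 7 remove the baseline adjustment it relies on, while the table footnotes keep it

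*SAP*

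**What the plan says.** Section 5 (Sample-size) rests the size of the trial on an analysis-of-covariance calculation and concludes that "a sample size of 94 individuals was required for this trial (47 per group), with 80% power and assuming a two-sided alpha of 0.05". The effect on which that calculation was based is described only as follows: it was meant "to detect a statistical significant 33% difference in pain scores between the intervention group and the control group". The section gives no SD, no difference in VAS points and no correlation between baseline and week 26.

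Section 6 (Covariates and Subgroups) says that covariates bring nothing to the analysis, and gives the double-blind randomised design as the reason. Section 7 (Primary and secondary outcome analysis) says of version 5 that "we found that adjusting for baseline and age did not enhance our analysis", gives the same reason, and takes the adjustment out.

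Section 13 says otherwise. The note under Table 3 describes linear mixed models fitted to the post-injection visits only, "Controlling for pain score (average past 4 weeks) at baseline and age at baseline". The footnote to the secondary-outcome table likewise keeps average pain and age at baseline in the model.

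On losses, Section 4 says "If withdrawal occurs before the injection, these patients will be replaced in order to reach the desired statistical power". Later withdrawals are censored at the last available time point.

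**The concern.** The sample size and the analysis should describe the same comparison. An ANCOVA sample size is smaller than the plain two-group size because the baseline covariate removes part of the outcome variance. If the covariate is then left out, that variance returns and the same number of participants gives less power.

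The reason given for leaving it out does not hold. Randomisation balances the arms in expectation, and blinding protects the assessment. Neither reduces the residual variance of the week-26 pain score, which is what adjustment for a prognostic baseline does.

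Two things are at stake. Two analysts could fit different primary VAS models, one following Section 7 and one following Table 3, and both could claim to have followed the plan. And a null result would be read against an 80% power that the analysis text does not support.

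**Working it through.** **Inputs from the SAP.** Two-sided alpha 0.05, power 80%, 47 per group, 1:1 allocation, ANCOVA method (Sections 4 and 5).

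**Assumed, because the SAP does not give it.** Correlation ρ between baseline and week-26 pain: 0.3, 0.5 and 0.7.

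**Step 1: the plan's own figure.** With z = 1.960 + 0.842 = 2.802 (z² = 7.849), the ANCOVA size per arm is

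n = 2 z² SD² (1 − ρ²) / δ².

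Without SD, δ in points and ρ, the 47 can be neither reproduced nor refuted. Some assumed inputs reach it. For example, with δ = 33% of a baseline of 5 = 1.65, SD 3 and ρ 0.3, n = 2 × 7.849 × 9 × 0.91 / 2.7225 = 47.2, rounded up to 48. Over baselines of 5 to 8, SDs of 2 to 3 and ρ from 0 to 0.7, n runs from 5 to 52 per arm.

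**Step 2: the effect implied by 47 per arm.** Take 47 as exactly right for 80% power under ANCOVA. Then

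δ / (SD √(1 − ρ²)) = √(2 × 7.849 / 47) = 0.578

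by the normal approximation (0.584 with the noncentral t; the powers below agree to the nearest percentage point either way).

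**Step 3: the same data without the covariate.** Power = Φ(d √(47/2) − 1.960), where

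- for the week-26 value alone, d = 0.578 √(1 − ρ²);
- for change from baseline, whose SD is SD √(2(1 − ρ)), d = 0.578 √((1 + ρ)/2).

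| Assumed ρ | d, week 26 | Power, week 26 | Per arm for 80%: 47/(1 − ρ²) | d, change | Power, change |
|---|---|---|---|---|---|
| 0.3 | 0.551 | 76% | 52 | 0.466 | 62% |
| 0.5 | 0.500 | 68% | 63 | 0.500 | 68% |
| 0.7 | 0.413 | 52% | 93 | 0.533 | 73% |

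For these two contrasts the direction does not depend on the value assumed. The week-26 comparison has less power than ANCOVA for any ρ above 0, and the change score has less for any ρ below 1. Only the size depends on ρ.

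**Step 4: the sections side by side.**

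| Place | Baseline pain in the model? |
|---|---|
| Section 5, sample size | Yes, implied by ANCOVA |
| Section 6, covariates | No |
| Section 7, outcome analysis | No |
| Section 13, Table 3 note | Yes, with age |
| Section 13, secondary-outcome table footnote | Yes, with age |

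**The case against.** A reader might infer that the trial is shown to have less than 80% power. The SAP does not support that, for four reasons.

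- **The figures are conditional.** They assume that 47 was exactly sufficient under ANCOVA, and they use a ρ that the SAP does not state. At ρ = 0 the week-26 comparison loses nothing; at 0.3 it loses 4 points.
- **The adjustment is not dropped everywhere.** If the table footnotes govern, the mismatch with Section 5 largely disappears. What is proven is a contradiction.
- **The planned model is not a two-sample test.** Section 7 plans a repeated-measures mixed model and does not fix the contrast. With baseline as one of the outcomes and a common baseline mean, the model would recover most of the ANCOVA efficiency. If the group effect were averaged over the four follow-up visits, with equal correlations and a constant effect, d would be 0.578 √(1 − ρ²) / √((1 + 3ρ)/4). Unadjusted power would then be about 97%, 87% or 62% at ρ 0.3, 0.5 or 0.7.
- **The power concerns the continuous VAS score.** Section 3 defines the primary endpoint as a responder criterion that combines VAS and PGI-I. Restoring the covariate would not establish 80% power for that endpoint.

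A reader might also infer that failing to allow for loss after injection is an error. With 10% or 20% complete-case loss, even full ANCOVA would fall to about 76% or 71%. But no loss rate is stated, the 94 may already contain an allowance, the protocol is not at hand, and the mixed model uses partial follow-up. Those figures are the pessimistic end.

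All of this limits the size of the claim. It does not touch the contradiction or the invalid reason for removal. Nor does the averaging argument favour leaving baseline out: at ρ = 0.5 the variance of the four-visit mean, in units of SD², is (1 + 3ρ)/4 = 0.625 unadjusted and 0.625 − ρ² = 0.375 adjusted. In addition, the null hypothesis in Section 7 is set at 26 weeks.

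**Conclusion.** The concern holds as an inconsistency between design and analysis. Section 5 counts on baseline adjustment, Sections 6 and 7 remove it for a reason that is not valid, and the footnotes in Section 13 keep it. The 80% power is therefore not supported by the analysis text.

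If 47 per group was exactly sufficient under ANCOVA and the contrast is an unadjusted one at week 26, power would be somewhere between 76% and 52% for ρ from 0.3 to 0.7, or between 62% and 73% for a change score. The actual shortfall cannot be determined from the SAP. No figure in Section 5 is shown to be miscalculated. The inputs missing from it may stand in the protocol and are not themselves a finding. Loss after injection is a secondary caveat.

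**What to change.** 1. In Section 7, restore baseline pain as a covariate in the continuous VAS mixed model, with age, as the footnotes already say. Alternatively, specify baseline as one of the outcomes with a mean common to both arms. Name week 26 as the contrast that answers the null hypothesis.
2. Delete the sentences in Sections 6 and 7 that remove covariates and the baseline and age adjustment, so that they agree with the footnotes in Section 13.
3. Keep the unadjusted model as a sensitivity analysis.
4. If the adjustment is to stay out, correct both footnotes instead and restate the Section 5 power for the unadjusted week-26 analysis, with the SD, point difference and correlation used.

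The cost is SAP wording only. Baseline pain is already collected, so no extra data or participants are needed. Because the SAP describes allocation in the past tense, the change should be dated and made before outcomes are compared by arm. It improves the precision of the VAS comparison. It leaves open the power for the responder endpoint and the effect of any loss after injection.

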1. Is the occurrence of missing data random, or is there a discernible pattern among these individuals?
2. What is the source of the missing data?
3. Is there any correlation with specific variables?
4. Can we identify a pattern in the missing data?

Based on the answers to these questions, the potential options for the pattern of missing data are as followed: Missing completely at random (MCAR), missing not at random (MNAR), and missing at random (MAR).

In case of additional analyses not performed using mixed models, missing data will be examined and if necessary randomly imputated.

Patients who are lost to follow-up will be censored at the last visit on which all assessments were completed.

- 1. Interim Analyses and Data Monitoring

No interim analyses are planned.

1. **Efficacy analyses**
   1. Timing of final statistical analysis

The statistical analyses of the primary outcome and secondary outcomes (measured 26 weeks after treatment) will be performed after a minimum of 26 weeks have elapsed from the inclusion of the final patient in the study and after data cleaning for these outcomes has been completed.

The statistical analysis of the follow-up study will be performed 26 weeks after inclusion of the final patient and data cleaning for these outcomes has been completed.

- 1. Primary and secondary outcome analysis

The null hypothesis entails that there is no significant difference in decrease of chronic pelvic pain scores 26 weeks after treatment between the intervention group receiving BTA injections and the control group receiving placebo injections among women with chronic pelvic pain.

VAS score Analysis:

- Mixed models for repeated measurements will be used. VAS scores will be compared over time between groups
- Primary endpoint: Percentage difference in VAS score between baseline and 26 weeks post-treatment will be calculated for each group.

PGI-I Analysis:

- Mixed models for repeated measurements will be used.
- PGI-I scores will be analyzed to identify differences between groups over time.
- Primary endpoint: the primary outcome of PGI-I scores being 1 or 2 (presented as median and interquartile (IQ) range) will be compared between groups.

Secondary outcome analysis

Questionnaire Scores:

- The total scores of all questionnaires will be analyzed over time using mixed models for repeated measurements.
- Analysis will involve assessing changes over time between groups MAPLe

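### The SAP's random-imputation rule carries no imputation uncertainty and may reach the 26-week responder comparison; its cut-off for women lost to follow-up discards observed scores and does not match the withdrawal rule

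*SAP*

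**What the plan says.** **Main approach.** SAP section 6 (Analysis considerations, Missing data) relies on mixed models: "We will use mixed models for repeated measurements and its ability to handle missing data effectively". It asks four questions about the pattern of missingness and lists MCAR, MAR and MNAR as possible answers, but ties no action to the answer.

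**Everything else.** For any additional analysis that does not use mixed models, the same section says that "missing data will be examined and if necessary randomly imputated".

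**Two cut-off rules.**
- Section 6, Missing data: "Patients who are lost to follow-up will be censored at the last visit on which all assessments were completed".
- Section 4 (Study methods, Replacement of individual subjects after withdrawal), for women who withdraw between injection and week 26: "the data will be censored at the last available time-point". Available data are then analysed in the intention-to-treat group.

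**The responder comparison.**
- Section 7 (Efficacy analyses) lists the primary-endpoint bullets for VAS and PGI-I under mixed-model headings.
- Section 10 (Comparison to study protocol) says "We will not use Kaplan Meier to estimate the success rates at 26 weeks of follow-up" and continues "Instead we will use the mixed models for repeated measurements".
- Table 3 in section 13 gives the responder rows as number and percentage per arm, and its footnote describes linear mixed models.
- Section 11 (Presentation of study results) says "Relative Risk or mean difference will be presented together with 95% confidence interval, and p-value otherwise as appropriate".

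**The concern.** A linear mixed model of scores gives mean differences. It does not directly give a responder count, a percentage or a relative risk, and the SAP names no binary model. Section 11 presents the primary outcome for everyone randomised, so a woman without week-26 data needs either an assigned status or a stated exclusion. The only rule in the SAP for analyses outside the mixed models is random imputation.

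If randomly drawn values are analysed as though they had been observed, the standard error ignores the draw. Depending on where the values are drawn from, the result is either intervals that are too short or a treatment difference pulled towards zero.

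The cut-off rule raises a second problem. The pain score is one item of painDETECT (section 12), so it can be present when another questionnaire is unfinished. Cutting at the last fully completed visit then removes pain and PGI-I scores that the woman did give. A likelihood-based mixed model could have used them, and they come shortly before she was lost.

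**Working it through.** **Inputs**
- From the SAP: 47 women per arm (section 5); post-baseline questionnaires at weeks 4, 8, 12 and 26 (section 4).
- Assumed, because the SAP gives none: 10% to 20% missing at week 26, missing completely at random; responder rate of 30% to 40% in both arms under the null; 30% versus 55% under an effect.

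The SAP states no figure on this point to reproduce. Its sample size serves only as the number per arm. It cannot be re-derived, because no SD, baseline mean, correlation or dropout rate is given.

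**A. One draw within arm, treated as observed.** With a fraction m missing, the arm's estimate is (1−m) times the observed proportion plus m times the imputed proportion. Its variance is approximately

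p(1−p)/n × [1/(1−m) + m],

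while the analysis uses p(1−p)/n. The ratio of nominal to true standard error is therefore 1/√[1/(1−m) + m].

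- m = 0.10: 1/√(1.111 + 0.10) = 0.909. Type I error = 2[1 − Φ(1.96 × 0.909)] = 7.5%.
- m = 0.20: 1/√(1.25 + 0.20) = 0.830. Type I error = 2[1 − Φ(1.96 × 0.830)] = 10.4%.

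Simulation at 47 per arm (pooled z test, Wald interval for the difference in proportions; 200,000 runs at 30% and 40% response, 20,000 at 35%) agrees:

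| Response in both arms | Type I error, 10% missing | Type I error, 20% missing | Coverage, 10% missing | Coverage, 20% missing |
|---|---|---|---|---|
| 30% | 7.6% | 10.6% | 91.7% | 88.7% |
| 35% | 7.6% | 10.5% | 91.9% | 88.9% |
| 40% | 7.2% | 10.3% | 92.4% | 89.3% |

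The same variance factor applies to each arm's log proportion, so to first order it carries over to the relative risk.

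**B. One draw from both arms pooled.** Imputed values have the same expectation in both arms, so the expected difference is (1−m) times the true one: 0.90 × 25 = 22.5 points and 0.80 × 25 = 20.0 points. In simulation (30% versus 55%), type I error stays near 5%, and coverage is 94.0% at 10% missing and 91.9% at 20%.

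**C. Alternatives, both arms at 30% response.** Multiple imputation within arm (50 imputations, Rubin's rules, 40,000 runs) gives type I error of 5.5% and 5.8%, and coverage of 94.5% and 94.2%, at 10% and 20% missing. Complete cases give 5.1% and about 94.3% at both rates.

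**D. What the cut-off removes.** It applies only to women lost to follow-up, and only to visits after the last complete one. Suppose one attended visit in six is incomplete, independently, and a lost woman attends up to three follow-up visits. The expected number of trailing incomplete visits is 1/6 + 1/36 + 1/216 ≈ 0.20 per lost woman. With 15% to 20% lost (14 to 19 of 94), that is 14 × 0.20 ≈ 3 to 19 × 0.20 ≈ 4 visits out of 94 × 4 = 376, or about 1%. The loss would be larger if incompleteness clusters just before a woman is lost.

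**The case against.** **Single imputation.** A reader might infer that the SAP prescribes single imputation. It does not: it says neither single nor multiple, and it imputes only if necessary. What stands is that the wording permits one draw and contains nothing that would carry the uncertainty.

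**The responder comparison.** A reader might infer that the rule definitely governs this comparison. Sections 7 and 10 point the other way, to mixed models, and the relative-risk sentence is generic, since section 11 repeats it for the secondary outcomes. Against that, Table 3 describes linear models and no binary model is named. The method is unassigned, which is less than saying that random imputation is assigned to it. The null hypothesis in section 7 concerns pain scores, and their mixed-model analysis is untouched by this rule.

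**False positives.** Excess type I error arises only with draws within arm. Pooled draws dilute the effect instead. The two harms are alternatives and should not be added together.

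**The cut-off.** A reader might infer that scores are lost whenever any questionnaire is unfinished. The rule covers only women lost to follow-up, and an incomplete visit followed by a complete one loses nothing. The two cut-off sentences also name different events, withdrawal and loss to follow-up, and cutting at the last available time-point discards nothing. But the SAP does not say how the two events are told apart, so the same woman could fall under either rule. Nor does it say why censoring language appears, so reading it as a remnant of the dropped Kaplan-Meier analysis would be conjecture.

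**The remedy.** Complete cases also hold their error rate under missingness completely at random. Multiple imputation is preferable because it uses the earlier visits and relies on a weaker missingness assumption.

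**Conclusion.** The point holds in this limited form, and the SAP should be changed before analysis. Two stated rules could worsen the results if followed. The imputation rule carries no uncertainty and may reach the responder comparison: a type I error of about 7.6% to 10.5% with coverage of about 92% to 89% under one draw within arm, or a 25-point difference reduced to 22.5 to 20 points under pooled draws. The loss-to-follow-up cut-off discards observed scores, probably a few visits, and does not match section 4.

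The sizes rest on 10% to 20% missing completely at random, on assumed responder rates, and on the rule being applied to the responder comparison in the way described. With less missing the effect is smaller: at 5% missing and 30% response, one draw within arm gives a type I error of 6.3%. If the responder comparison is analysed with a suitable binary mixed model, the imputation harm does not arise there.

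**What to change.** 1. In section 6, replace the loss-to-follow-up sentence with a statement that all observed values of each outcome enter its model, whether or not other assessments at that visit were completed. Align the withdrawal sentence in section 4 with it.
2. Name the estimator and test for the 26-week responder comparison, including how the relative risk and its interval are obtained.
3. Replace random imputation with multiple imputation by arm (for example 50 imputations), using baseline and all observed VAS and PGI-I visits. Impute the week-26 scores, derive responder status afterwards, and combine with Rubin's rules.
4. Add one sensitivity analysis counting women with missing week-26 data as non-responders.

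The cost is revised SAP wording and a few lines of R, which is already among the planned software. Intervals will be slightly wider than under a single draw, and there is a little more analysis to run and report.
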